# Prophylactic platelet transfusion prior to central venous catheter placement in patients with thrombocytopenia: study protocol for a randomised controlled trial

**DOI:** 10.1186/s13063-018-2480-3

**Published:** 2018-02-20

**Keywords:** Central venous catheter, Thrombocytopenia, Platelet count, Bleeding complication

## Abstract

**Background:**

Severe thrombocytopenia should be corrected by prophylactic platelet transfusion prior to central venous catheter (CVC) insertion, according to national and international guidelines. Even though correction is thought to prevent bleeding complications, evidence supporting the routine administration of prophylactic platelets is absent. Furthermore, platelet transfusion bears inherent risk. Since the introduction of ultrasound-guided CVC placement, bleeding complication rates have decreased. The objective of the current trial is, therefore, to demonstrate that omitting prophylactic platelet transfusion prior to CVC placement in severely thrombocytopenic patients is non-inferior compared to prophylactic platelet transfusion.

**Methods/design:**

The PACER trial is an investigator-initiated, national, multicentre, single-blinded, randomised controlled, non-inferior, two-arm trial in haematologic and/or intensive care patients with a platelet count of between 10 and 50 × 10^9^/L and an indication for CVC placement. Consecutive patients are randomly assigned to either receive 1 unit of platelet concentrate, or receive no prophylactic platelet transfusion prior to CVC insertion. The primary endpoint is WHO grades 2–4 bleeding. Secondary endpoints are any bleeding complication, costs, length of intensive care and hospital stay and transfusion requirements.

**Discussion:**

This is the first prospective, randomised controlled trial powered to test the hypothesis of whether omitting forgoing platelet transfusion prior to central venous cannulation leads to an equal occurrence of clinical relevant bleeding complications in critically ill and haematologic patients with thrombocytopenia.

**Trial registration:**

Nederlands Trial Registry, ID: NTR5653 (http://www.trialregister.nl/trialreg/index.asp). Registered on 27 January 2016. Currently recruiting. Randomisation commenced on 23 February 2016.

**Electronic supplementary material:**

The online version of this article (10.1186/s13063-018-2480-3) contains supplementary material, which is available to authorized users.

## Background

Central venous catheter (CVC) placement is a frequently applied medical intervention that enables both monitoring and treatment of patients [1, 2]. The inserted cannula provides central venous access either in the neck region (subclavian vein or jugular vein) or groin region (femoral vein). CVCs form an essential element of treatment in various patient categories, mainly haematologic and intensive care patients [1, 2]. The latter patient categories have an elevated risk for a low platelet count (thrombocytopenia), due to their treatment and the physiopathology of their illnesses [3–5]. Thrombocytopenia is associated with an increased bleeding risk for many invasive procedures [6]. However, abnormal traditional coagulation tests are known to be a poor predictor of peri-procedural bleeding [7–9]. Current national and international guidelines are conflicting, most recent Dutch and UK guidelines support prophylactic platelet transfusion below a platelet count of 50 × 10^9^/L, prior to CVC placement [10, 11]. Others support the administration of prophylactic platelet transfusion below a platelet count of 20 × 10^9^/L; however, the evidence supporting these recommendations is of low quality [12, 13]. Current prophylactic platelet transfusion practice prior to CVC placement varies widely [14].

In the last decades, more has become known about transfusion-related morbidity and mortality; platelet transfusion bears a substantial risk for morbidity and mortality, including transfusion-related acute lung injury (TRALI), transfusion-associated cardiac overload (TACO), allergic reactions, allo-immunisation and transfusion-related infections [15–21]. In a prospective cohort study of consecutive intensive care unit (ICU) patients receiving blood transfusion products, 6% developed TACO [22]. In the Netherlands, 0.32% of pooled platelet concentrates and 0.23% of apheresis platelet concentrate units are contaminated with bacteria [23]. Transfusion of platelets is an independent risk factor for the onset of nosocomial infections in ICU patients, with a hazard ratio of 1.40 (95% confidence interval (CI) 1.2–1.8) [24]. Next to the burden of transfusion exposure, blood products are expensive and scarce. Critically ill and haematologic patients are at higher risk of transfusion-related morbidity and mortality [15, 25]. Altogether, these insights in transfusion-related morbidity and mortality have made platelet transfusion without a very strict indication less desirable.

Recent retrospective studies suggest that the experience of the physician and the technique used (ultrasound (US) vs. landmark) rather than the platelet count predicts bleeding complications [26–28]. The introduction of US guidance for CVC placement was a major improvement [29]. The use of US for CVC insertion results in a lower number of puncture attempts, arterial puncture, haematoma pneumothorax and haematothorax [29–31]. One meta-analysis showed a lower incidence of arterial puncture with the use of US, namely 37/2009 (1.8%), compared to 196/2018 (9.7%) with anatomical landmarks (RR 0.25, 95% CI 0.15 to 0.42). Also, the occurrence of haematoma was reduced from 113/1512 (7.5%) to 24/1500 (1.6%), with a RR 0.30 (95% CI 0.19 to 0.46) [31].

Consequently, recent retrospective studies suggest that US-guided central venous cannulation can safely be performed in patients with a platelet count above 20 × 10 ^9^/L [28, 32, 33]. In a study with 604 CVC placements, in 193 patients with acute leukemia, manual compression to stop bleeding was required in eight patients, no major bleeding was observed [28]. However, this study missed a control group and the administration of prophylactic platelet transfusion was not standardised, resulting in high risk of bias.

The current protocol describes the first randomised controlled trial to evaluate the effect of prophylactic platelet transfusion in haematologic and intensive care patients in need of a CVC.

## Methods/design

### Study hypothesis

We hypothesise that the improved standards of CVC placement, e.g. the use of US, make the need for correction of thrombocytopenia prior to CVC placement obsolete.

### Study objective

The primary objective is to demonstrate that the omission of prophylactic platelet transfusion in severely thrombocytopenic patients does not increase the amount of bleeding complications related to CVC placement.

### Primary endpoint

A procedure-related relevant bleeding, occurring within 24 h after the procedure. A WHO grade of 2–4 (Additional file 1) up to 24 h of randomisation is defined as relevant bleeding.

### Secondary endpoints

• Platelet transfusion requirements within 24 h of CVC placement

• Number of RBC transfusions within 24 h of CVC placement

• WHO grade-1 bleeding within 24 h of CVC placement

• Haematoma size

• Haemoglobin level at 1 h and 24 h after CVC placement

• Platelet transfusion increment

• HEME bleeding score (Additional file 1)

• Allergic transfusion reaction within 24 h

• Onset of acute lung injury within 48 h

• Length of hospital stay

• Costs

### Design

The PACER trial is a randomised controlled, non-inferiority trial on prophylactic platelet transfusion prior to CVC placement in patients with severe thrombocytopenia. It is an investigator-initiated, multicentre, parallel, randomised controlled, two-arm trial in haematologic and/or intensive care patients with thrombocytopenia and an indication for CVC placement. The PACER trial will be conducted according to the principles of the Declaration of Helsinki as stated in the current version of Fortaleza, Brazil, 2013 [34] and in accordance with the Medical Research Involving Human Subjects Act (WMO). The Institutional Review Board of the Academic Medical Centre, Amsterdam, the Netherlands, approved the trial protocol under reference number 2015_27#B201662. The trial is registered at http://www.trialregister.nl/trialreg/admin/rctview.asp?TC=5653 (NTR5653). Intensive care patients will be provisionally included under a strategy of deferred consent, which is explained in detail in the ‘Consent’ section below. For patients at the Department of Haematology, written informed consent is obtained prior to randomisation. We adhered to the SPIRIT statement (Additional file 2 SPIRIT checklist).

### CONSORT diagram

The Consolidated Standards of Reporting Trials (CONSORT) diagram of the PACER study is presented in Fig. 1. Consecutive thrombocytopenic patients who have an indication for central venous catheterisation are screened. Demographic data are registered regardless of meeting enrolment criteria using a predefined screen log. If patients are excluded for participation, the reason(s) for exclusion are registered. For the screening of thrombocytopenia, routinely conducted laboratory values are used. The indication for a CVC is determined at the physician’s discretion.

**Fig. 1 Fig1:**
[figure not shown]
PACER trial (Consolidated Standards of Reporting Trials (CONSORT)) Diagram. CONSORT diagram of PACER. For haematologic patients, informed consent is required prior to randomisation. For the intensive care patients, randomisation takes place via deferred consent. If consent is not obtained, data are excluded

### Setting

The PACER trial is a multicentre study performed in six academic and five teaching hospitals in the Netherlands. We plan to include 392 patients in 36 months, with a potential limit of 462 patients to accommodate loss to follow-up and possible dropout.

### Study population

Thrombocytopenic patients with a platelet count of 10–50 × 10^9^ are eligible for participation if a central line is indicated. Both patients who need elective and emergency line insertions are appropriate for randomisation. Both tunnelled and non-tunnelled CVCs are suitable for inclusion, as well as lines inserted for continuous venovenous haemodiafiltration. Notably, patients requiring replacement of central catheters are also eligible. Patients can participate in the study multiple times; however, a patient can be randomised once per 24 h. The CVC should be expected to be in situ for at least 24 h to monitor 24-h bleeding complications. Therefore, central lines for single plasmapheresis or the harvesting of stem cells will not be included. All other indications can be included, e.g. inotrope medication, lack of peripheral venous access, haemodialysis, haemodynamic monitoring, administration of irritating medication such as chemotherapy. According to guidelines, patients with an International Normalised Ratio (INR) of > 1.5 before line placement are excluded [35]. However, patients are eligible after correction of an elevated INR with fresh frozen plasma or prothrombin concentrate. Non-adult patients (age below 18 years) are excluded, as are patients with a history of congenital or acquired coagulation factor deficiency or bleeding diathesis. Also patients on therapeutic anticoagulant therapy are excluded. Of note, patients with a single platelet aggregation inhibitor and/or therapeutic unfractionated heparin that is discontinued at least 1 h prior to insertion are considered to be eligible.

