### Follow-up

The follow-up time for the primary outcome is 24 h. Patient information about both ICU and hospital discharge or death, whichever comes first, are collected.

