### Statistical considerations

We target to include 392 patients, with a potential limit of 462 patients to accommodate loss to follow-up and a possible dropout. The expected rate of severe peri-procedural bleeding incidents is around 0% [28, 33, 41–43]. Major bleeding is defined as WHO grade 3: gross blood loss requiring transfusion, or grade 4: debilitating blood loss (Additional file 1: Table S1). Considering the low complication occurrence, sample sizes that are by far unrealistic within the proposed study are required to demonstrate non-inferiority with an acceptable non-inferiority limit of (< 1%). We therefore also include WHO grade-2 bleedings in the definition of the primary outcome. As the observed bleeding events will concern predominantly grade-2 bleedings, and probably no or only incidental bleedings with more severe grades 3 or 4, an upper limit reflecting an absolute risk increase of 2.5% more bleeding events as the criterion to statistically demonstrate non-inferiority is considered both statistical and clinical acceptable. The sample size is increased by 2% to correct for loss to follow-up and by 15% to correct for dropouts, e.g. refusal of consent. Using a non-inferiority design, a sample size of 196 patients (per arm) and a percentage bleeding events of 1% in the control group and an expected percentage bleeding events of 1% in the experimental group will result in a power of 80% to exclude that there is a significant bleeding rate in the experimental arm (> 3.5% bleedings, absolute risk increase 2.5%, two group *t* test with a 0.05 two-sided significance level). As we do not anticipate any loss to follow-up – considering the short time-span of the study – we therefore intend to enrol 392 patients in total.

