### Statistical analysis

Statistical analysis will be based both on an intention-to-treat principle and a per-protocol approach. Baseline assessments and outcome parameters will be summarised using simple descriptive statistics. The main analysis focusses on a comparison between the trial treatment groups of the primary outcome, the occurrence of relevant bleedings, expressed in a relative risk estimate and absolute risk increase, with the associated 95% upper confidence limit. Non-inferiority is demonstrated if this interval does not exceed the non-inferiority limit of 2.5% absolute difference in favour of transfusion.

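### Repeat randomisation leaves the unit behind the 392 undefined and lets 48-h lung injury and admission-level outcomes count in both arms

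*Protocol article*

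**What the plan says.** Under Study population, the protocol article allows repeat entry: "Patients can participate in the study multiple times; however, a patient can be randomised once per 24 h". The same section foresees a common route to it: "Notably, patients requiring replacement of central catheters are also eligible".

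The trial is counted in patients. Setting says "We plan to include 392 patients in 36 months, with a potential limit of 462 patients". Statistical considerations gives 196 patients per arm from a two-group t test, assuming "a percentage bleeding events of 1% in the control group" and the same rate in the experimental group, with a 2.5-point margin.

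Statistical analysis describes a "comparison between the trial treatment groups of the primary outcome", reported as a relative risk and an absolute risk increase with a 95% upper limit. The Participant timeline section adds multiple logistic regression on patient, procedure, catheter and transfusion characteristics. Neither section mentions repeat inclusions.

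Some outcomes run longer than one inclusion. Secondary endpoints lists "Onset of acute lung injury within 48 h", hospital stay and costs. The Participant timeline section adds ICU stay and ICU and hospital mortality. Follow-up states: "Patient information about both ICU and hospital discharge or death, whichever comes first, are collected".

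**The concern.** Two things follow from allowing repeats while planning as if there were none.

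First, the 392 has no defined unit. If it counts inclusions, some come from the same patient and may be correlated, whereas the sample size formula treats them all as independent. In a non-inferiority trial, an understated standard error makes it easier to declare non-inferiority.

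Second, and independently of any assumed correlation, some outcomes cannot be attached to one arm. The 24-h bleeding endpoint roughly matches the 24-h interval between randomisations. The 48-h lung-injury window does not, and stay and mortality belong to the admission rather than to the catheter. The Background section motivates the trial partly by transfusion harms, including transfusion-related lung injury. These secondary outcomes are where such harms would appear, and putting the same patient in both arms hides a difference.

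**Working it through.** **1. The plan's own figure.** Inputs from Statistical considerations: 1% in each arm, margin 0.025, power 80%.

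n per arm = (z_alpha + z_power)² × 2 × 0.01 × 0.99 / 0.025²

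With one-sided 0.05: (1.645 + 0.842)² × 31.68 = 196. The stated figure is reproduced with all 392 observations independent. With one-sided 0.025, which is what the two-sided 0.05 label would mean, the result is 249; that is a separate matter.

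**2. What 392 could mean.** The repeat rate is not given. If 392 counts inclusions, 1.25, 1.5 or 2 inclusions per patient correspond to 392/1.25 = 314, 392/1.5 = 261 or 392/2 = 196 distinct patients.

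**3. Effect on the primary comparison.** The number of inclusions per patient (m) and the within-patient correlation (ICC) are both assumptions.

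*Upper bound, all of a patient's inclusions in the same arm.* Design effect = 1 + (m − 1) × ICC; power is recomputed at 196 / design effect.
- m = 1.25, ICC 0.1: 1.025, power 0.792
- m = 1.5, ICC 0.3: 1.15, power 0.750
- m = 2, ICC 0.3: 1.30, power 0.704

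*Simulation.* 392 inclusions, 4,000 runs per scenario, naive Wald upper limit at one-sided 0.05, ICC 0.3. A mean of 1.25 is 80/15/5% of patients with 1/2/3 inclusions; a mean of 1.95 is 50/20/15/15% with 1/2/3/4. Type I error is taken at 3.5% v 1%, power at 1% v 1%.

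| Scenario | SD/naive SE, 3.5% v 1% | Type I error | SD/naive SE, 1% v 1% | Power |
|---|---|---|---|---|
| No repeats | 0.997 | 0.083 | 1.000 | 0.807 |
| Mean 1.25, randomised anew | 1.001 | 0.082 | 0.999 | 0.810 |
| Mean 1.95, randomised anew | 1.069 | 0.100 | 0.985 | 0.802 |
| Mean 1.25, same arm kept | 1.073 | 0.092 | 1.075 | 0.789 |
| Mean 1.95, same arm kept | 1.196 | 0.122 | 1.200 | 0.780 |

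The simulation error of a type I rate near 0.08 is √(0.08 × 0.92 / 4000) = 0.004. Without repeats the rate is already 0.075 to 0.083 across four runs, because events are rare: 196 × 0.01 is about 2 per arm.

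When each inclusion is randomised anew, same-arm pairs add variance and opposite-arm pairs remove it. The two cancel when the arms have equal rates and only partly when they differ. This is why 1.07 appears at the margin and not under equality.

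**4. Attribution of lung injury.** Take the 48 h as running from inclusion (the origin is not stated). A patient is randomised to transfusion at 0 h, with a window of 0 to 48 h. The patient is randomised again at 24 h, to no transfusion, with a window of 24 to 72 h. The windows share 48 − 24 = 24 h. Lung injury at 30 h falls in both, once in each arm. In the reverse order, an injury following the second, transfused inclusion falls inside the window of the first, untransfused one.

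**5. Attribution of admission-level outcomes.** Hospital stay and mortality have one value per admission. A patient randomised once to each arm in one admission contributes that value to both arms, and so adds nothing to the difference between them.

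**6. What is not affected.** The economic evaluation in the Participant timeline section uses cost per procedure-related bleeding event and per transfusion avoided. Costs of a single procedure or transfusion can be tied to one inclusion.

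**The case against.** **The analysis plan may deal with it.** Statistical analysis names no variance estimator, so independence in the main analysis is inferred, not stated. Only a condensed article is at hand, and clustering may be handled in the analysis plan. This stands as far as the variance method goes. It does not remove what the article itself fixes: repeat entry, a count in patients from an independent-observation formula, and a 48-h outcome with a 24-h re-randomisation interval.

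**392 may mean distinct patients.** Then repeats add information. At 1.25 inclusions per patient and ICC 0.3, the effective number is 392 × 1.25 / 1.075 = 456 even with every repeat in the same arm. This stands, and it shows that the unit is ambiguous.

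**A stronger reading is tempting but unsupported.** A reader might infer that the trial is underpowered. The leukaemia cohort in the Background section had 604 placements in 193 patients, about 3.1 each. With ICC 0.3 the design effect is 1 + 2.1 × 0.3 = 1.63, and power drops to about 62%. The arithmetic is correct, but it needs every repeat in the same arm, a repeat rate from a different population, an assumed correlation, and 392 read as inclusions. The protocol says that the patient is randomised each time and describes no rule carrying the first allocation forward.

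**The attribution problem is narrow.** It touches only patients re-randomised to the other arm within 48 h (lung injury) or within one admission (stay, mortality, admission-level costs). Catheters must be expected to stay at least 24 h, which may make very early repeats uncommon. These outcomes are secondary, since the stated objective concerns bleeding. All of this stands and limits the weight of the point.

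**Conclusion.** The concern holds in a limited form and should be corrected.

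For the primary risk difference, the likely effect is small if each inclusion is randomised anew: a ratio of true to naive standard error of about 1.00 to 1.07, for an assumed 1.25 to 1.95 inclusions per patient and a correlation of 0.3. The upper end raises the simulated type I error to 0.100, from about 0.08 without repeats. No power loss is shown, because the documents give neither the repeat rate nor the correlation.

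The firmer finding needs no such assumption. Up to 24 of the 48 h for lung injury can overlap with the next inclusion, and outcomes with one value per admission have no single arm for a patient randomised to both. Both blur the arms towards no difference. How many patients this concerns cannot be derived from the documents, so the size of the dilution is unknown.

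It would be too broad to conclude that these outcomes cannot be assigned for the trial as a whole. Patients with a single inclusion are unaffected. So are stay and mortality when repeats fall in separate admissions, and procedure-level costs throughout.

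**What to change.** 1. State that the unit of randomisation and analysis is the CVC placement, and say whether the 392 counts placements or distinct patients.
2. Compute the primary upper limit allowing for within-patient correlation, by a method suited to rare events. One example is a score-type limit for the risk difference with the variance adjusted over a prespecified range of correlations. With about 2 expected events per arm, an identity-link GEE with robust variance is fragile. A patient-level bootstrap is little better: with 2 events among 196 unrepeated patients, an arm is redrawn with none in (194/196)^196, or about 13%, of samples.
3. Add a sensitivity analysis restricted to each patient's first inclusion.
4. Analyse 48-h lung injury by the patient's first randomisation, and stay, mortality and admission-level costs by the first randomisation in each admission.
5. Report how many patients were re-randomised to the other arm within 48 h or within the admission. Step 4 removes the double counting but not this contamination, since a patient can still receive the other strategy inside the first window.

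The cost is analysis wording and a small loss of observations for those secondary outcomes. Recruitment and treatment do not change.
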